**SUMMARY**

*Rationale:* the risk for weight regain after weight loss is high because the energy requirement for weight maintenance goes down and is lower than predicted from the new body composition after weight loss. Individual differences in weight regain, due to storing instead of oxidizing dietary fat, appear to be largely genetically determined.

*Objective:* to demonstrate differences in response of subjects with a high, low or medium predisposition for weight regain after weight reduction in terms of: body composition; energy expenditure; physical activity; and adipogenic capacity.

*Study design:* the study is a weight-loss and -maintenance study, with a parallel design. Groups will be stratified according to the subjects’ genetic profile for established markers of postprandial responses in substrate utilization and habitual physical activity.

*Study population:* the study population will consist of 200 healthy male and female subjects with a BMI 28-35 kg/m2 and age 18-50 y. Two subgroups of the study population with a high and low predisposition for weight regain will consist of 40 subjects per group, whereas the group with a medium predisposition for weight regain will consist of 120 subjects.

*Intervention:* subjects undergo a weight loss program, which consists of a very low energy diet (VLED; Modifast) containing 2.1MJ/d for 2 months, followed by a weight maintenance period of 10 months. Two subgroups of subjects with a high or low predisposition for weight regain will be studied more thoroughly during the weight maintenance period. Body weight, height, waist and hip circumference, dietary restraint, disinhibition, hunger, physical activity levels, blood parameter, polymorphisms, body composition, adipocytes, habitual physical activity, energy expenditure are measured.

*Main study parameters/endpoints:* the role of the genetic background involved in weight regain through mechanisms including energy expenditure, physical activity and adipogenic capacity.

*Nature and extent of the burden and risks associated with participation, benefit and group relatedness:* All subjects visit the university six times. The time burden for each subject depends on whether they belong to the high or low predisposition group or not. For all subjects there is a screening of around 45 minutes. Four visits for the group with medium predispositio, and therefore limited measurements (body weight, waist and hip circumference and body composition), will take 60 minutes and one visit of 20 minutes. In total these subjects need to stay at the university for approximately 305 minutes (=5h). Three visits for the subjects in the groups with a high/low predisposition for weight regain will take one night and the subsequent morning, so approximately 16h. The other two visits will be 20 and 60 minutes. In total these subjects need to stay at the university for approximately 50h. There are no risks for the subjects in consuming the VLED (Modifast, together with the recommended fruit and vegetables) as the macronutrient composition and vitamins/minerals content meet the Dutch recommended daily allowance. This VLED will demand some energy from the subjects at home. However, losing weight is a great advantage for these subjects, so probably they have enough will-power to complete these 2 months VLED. There is a risk of minor bruising during blood sampling. Deuterium is an isotope of water that naturally appears in the body. Drinking it does not expose the subject to any risks. The doubly labelled water is safe to use in humans since the water is labelled with stable isotopes. The concentrations of the samples are with an enrichment of 100 to 200 ppm far below 10000 ppm or 1%, where effects on biological systems have been observed. Collection of urine at home is only a minor time burden for the subjects. Studies in the respiratory chamber will be conducted using standard operating procedures. A pair of subjects will always participate in the study at the same time and therefore they will never be alone. The subjects will be able to contact the investigators during the entire night. In addition, they will be able to get out of the chamber at any time they feel uncomfortable. Taking a fat biopsy will be done under local anaesthetic, which only gives a very brief tingling pain at the site of infiltration under the skin. Local anaesthesia occurs with most standard clinical procedures in which this is used, resulting in minimal risks. Allergies for local anaesthetics will be one of the exclusion criteria. The biopsy itself can give a mild soreness and bruising near the biopsy site. Minimal scarring rarely occurs. Wearing the Tracmor will not have any risk and only minor time burden.

# INTRODUCTION AND RATIONALE

Weight regain is a common feature after weight loss treatments for obesity. The risk for weight regain is high, because the energy requirement goes down and is lower than predicted from the new body composition after weight loss (1). Individual differences in weight (re)gain appear to be largely genetically determined. Many studies identified genes associated with obesity (2, 3), whereas gene-environment interaction in relation to weight changes has been studied less frequently. Moreover, most of these studies only focussed on weight loss, instead of weight regain and weight maintenance. Therefore, we want to study weight maintenance after weight loss in subjects with a high, low and medium predisposition for weight regain based on their genetic profile.

Several candidate gene polymorphisms involved in weight management are already identified. A well-known example is the single nucleotide polymorphism (SNP) rs993909 in the fat mass and obesity-associated (FTO) gene (4-8). The A allele is associated with increased body mass index (BMI) (6). It has been suggested that FTO influences adiposity by affecting appetite. Indeed, the TA/AA genotype predisposes individuals to a reduced postprandial response in hunger and satiety (4). The Pro12Ala polymorphism of the peroxisome proliferators-activated receptor gamma 2 (PPAR2) is also strongly associated with weight management and specifically with weight maintenance (2, 3). The frequency distribution for the PPAR2 genotypes is different between subjects successful in weight maintenance after weight loss and subjects unsuccessful in weight maintenance after weight loss (9), with less heterozygous individuals in the successful group compared to the whole group. Weight regain was significantly greater in women with the Ala12 allele than women homozygous for the Pro12 allele (9, 10). The susceptibility towards weight regain in the Ala12 carriers might be due to decreased fat oxidation. Another polymorphism that shows specific associations with weight maintenance is the Arg16Gly polymorphism in the beta 2 adrenoreceptor (ADRB2) gene (2, 3). Individuals with weight regain more frequently had the Gly16 allele for the ADRB2 polymorphism compared to subjects who exhibited 24-month maintenance of weight loss (11). Polymorphism in the perilipin (PLIN) gene has also been associated with weight management, although women seem to be more sensitive to the genetic effects of perilipin than men (2, 3, 12). Obese patients carrying the 11482A allele have shown to be resistant to one-year weight management programme with a low-energy diet (13). Polymorphisms in the uncoupling proteins (UCPs) have been shown to influence exercise efficiency, resting energy expenditure (REE), substrate oxidation and body weight change. For example, the A3826G polymorphism in the UCP1 gene has been linked to lower weight loss response to a 25% reduction in energy intake, in which GG homozygotes were more resistant to weight loss (14). For the beta 3 adrenoreceptor (ADRB3) Trp64Arg polymorphism carriers of the Arg64 allele have shown to be more resistant to weight loss (2, 3). Other polymorphisms have been associated with biological or behavioural factors involved in weight management, like the AG/GG carriers in rs2267668 and AC/CC carriers in rs2076168 of the PPAR gene showed less physical activity than the AA carriers (15). The rs8192678 SNP in PPAR co-activator 1 (PPARC1) was also associated with physical activity, with GA/AA carriers spending more time on high-intensity physical activity than GG carriers (15). Certain SNPs have been shown to influence postprandial responses. Like the postprandial response in plasma ghrelin levels have been associated with SNPs in peptide YY (PYY) gene (215G>C) and the leptin receptor (LEPR) gene (326A>G and 688A>G), and in plasma PYY levels with SNPs in LEPR gene (668A>G) and neuro-peptide Y 2 receptor (NPY2R) gene (585T>C) (16). Also dietary restraint and disinhibition were associated with a SNP (477G>A) in the ghrelin receptor (GHSR) gene (16).

Genes interact with and exert their effects on various biological, behavioral and environmental factors, thereby influencing body weight and composition. It has been hypothesized that a reduced capacity to oxidize fat is involved in the development of obesity (1). Rats with inherited susceptibility to diet-induced obesity showed a reduced capacity for fat oxidation than rats resistant to diet-induced obesity (17). It has been suggested that the susceptibility to diet-induced obesity was based on a limitation in transporting fatty acids into hepatocytes an in initiating -oxidation of fatty acids. Also, the partitioning of dietary fat between tissues might play a role in the susceptibility to obesity (18). It has been shown that dietary fat oxidation is negatively related to body fatness, in which obese individuals showed the lowest fat oxidation (19). In obesity-prone rats weight regain after weight loss was accompanied by reduced oxidation of dietary fat and the formation of new adipocytes (20). In addition, with weight loss a major saving on energy expenditure has been found, mainly caused by a reduction in physical activity (1). This decrease in activity energy expenditure during energy restriction is difficult to overcome with exercise training (21). Resting energy expenditure (REE) and sleeping metabolic rate (SMR) has been shown to decrease during weight loss, but whether this also holds during weight maintenance is still subject of debate (22, 23). Finally, weight loss maintenance has been shown to depend largely on psycho-behavioural factors such as eating behaviour. These factors are also influenced by, and interact with genes. Like the disinhibition score as defined by the Three Factor Eating Questionnaire (TFEQ; (24)), was strongly linked to the gene coding for PPAR (3, 25). All these factors are likely to change during weight loss and maintenance. Therefore, adipogenic capacity, energy expenditure, physical activity and behavioural factors should all be investigated in a weight loss and maintenance experiment.

In summary, the risk for weight regain after weight loss is a major problem for the current obesity treatments, and is largely genetically determined. It is believed that an elucidation of the genetic component in the prognosis of weight management could assist in the development of more effective and individually tailored treatments. However, current research on the genetic component of weight management, and in particular weight regain, is still limited and data available are sometimes inconsistent. The current research proposal aims to identify groups with a high, low and medium predisposition for weight regain, based on a genetic profile and to demonstrate differences in the response of these subjects to a weight maintenance period after weight reduction in terms of body composition, physical activity, adipogenic capacity and energy expenditure.

# OBJECTIVES

Primary Objective:

To identify groups with a high, low and medium predisposition for weight regain, based on a genetic profile and to demonstrate differences in the response of these subjects to a weight maintenance period after weight reduction in terms of body composition, energy expenditure, physical activity, and adipogenic capacity.

Secondary Objective(s):

Not applicable

# STUDY DESIGN

Subjects screened for participation

Subjects excluded because they did not met inclusion criteria

Subjects included follow weight loss program

2 months (n = 200)

Highest predisposition for weight regain-group (n = 40)

 All measurements

Lowest predisposition for weight regain-group (n = 40)

 All measurements

Weight maintenance period of 10 months

Medium predisposition for weight regain (n = 120)  limited measurements

Fig 1. Flow of participants through the study

Subjects will be assigned to a subgroup based on their genetic profile, which will be determined with genotyping analysis from the blood drawn during the screening (for detail see section 7.3). The three groups will consist of subjects with a high predisposition for weight-regain, a low predisposition for weight regain and all subjects in between. All subjects undergo a weight loss program, followed by a weight maintenance period. The subjects in the group of low and high predisposition for weight regain will be studied more thoroughly, while the others will only undergo the more basal measurements. Figure 2 and 3 give an overview of all the measurements that will be done in the groups with a high/low predisposition for weight regain and the group with medium predisposition respectively (for details of the measurements see section 7.3).

|  | **Screening** | **Pre-weight loss** | **Weight reduction program (2 months)** | **Post-weight loss** | **Weight maintenance program (10 months)** | **Post-weight maintenance** |
| --- | --- | --- | --- | --- | --- | --- |
| Measurements |  | Month 0 | Months 1 | Month 2 | 3 months after start maintenance | 10 months after start maintenance |
| **Body weight**  **Height**  **Body mass index**  **Waist/Hip** | X  X  X  X | X  X  X | X  X  X | X  X  X | X  X  X | X  X  X |
| **TFEQ**  **Baecke** | X  X | X  X | X  X | X  X | X  X | X  X |
| **Total Body Water**  **Body density** |  | X  X |  | X  X | X  X | X  X |
| **SMR**  **BMR** |  | X  X |  | X  X |  | X  X |
| **Physical activity** |  | X |  | X | X | X |
| **Doubly labelled water** |  | X |  | X |  | X |
| **Blood parameters**  **Polymorphisms** | X  X |  |  |  |  |  |
| **Adipocytes** |  | X |  | X |  | X |
| **Time** | 45 min | 16h | 20 min | 16h | 60 min | 16h |

Fig 2. Measurements for the group with a high and low predisposition for weight regain. Three Factor Eating Questionnaire (TFEQ), Sleeping metabolic rate (SMR), basal metabolic rate (BMR).

|  | **Screening** | **Pre-weight loss** | **Weight reduction program (2 months)** | **Post-weight loss** | **Weight maintenance program (10 months)** | **Post-weight maintenance** |
| --- | --- | --- | --- | --- | --- | --- |
| Measurements |  | Month 0 | Month 1 | Month 2 | 3 months after start maintenance | 10 months after start maintenance |
| **Body weight**  **Height**  **Body mass index**  **Waist/Hip** | X  X  X  X | X  X  X | X  X  X | X  X  X | X  X  X | X  X  X |
| **TFEQ**  **Baecke** | X  X | X  X | X  X | X  X | X  X | X  X |
| **Total body water**  **Body density** |  | X  X |  | X  X | X  X | X  X |
| **Physical activity** |  | X |  | X | X | X |
| **Blood parameters**  **Polymorphisms** | X  X |  |  |  |  |  |
| **Time** | 45 min | 60 min | 20 min | 60 min | 60 min | 60 min |

Fig 3. Measurements for the group with medium predisposition for weight regain. Three Factor Eating Questionnaire (TFEQ).

# STUDY POPULATION

## Population (base)

The study population will consist of 200 healthy, non-smoking, overweight (BMI 28-35 kg/m2), males and females of 18-50 years of age. Recruitment will take place by advertising around the campus and in local newspapers.

Interested candidates will be sent the information brochure of the study, including the main inclusion criteria. In case the potential subject wants to participate and meets the main inclusion criteria, an appointment will be set for a screening visit.

During the screening:

- An informed consent form needs to be signed by the subject.
- Determination of weight and height, calculation of the Body Mass Index (BMI).
- Determination of waist and hip circumferences.
- Blood will be drawn to determine polymorphisms.
- Assessment of medical situation at the present time and in the past.
- Assessment of eating pattern by the Dutch translation of Three Factors Eating. Questionnaire (TFEQ). This questionnaire consists of three subscales: cognitive restraint of eating, disinhibition of dietary restraint and emotional eating, and perceived hunger.
- Assessment of habitual physical activity by a Dutch translation of the Baecke questionnaire. This questionnaire consists of three subscales: work activity, sports activity and non-sports leisure activity.

The results of the measurements of the physical parameters as well as the completed questionnaires will be checked on the inclusion and exclusion criteria before assigning the subject to the study population. The results concerning the polymorphisms will be used to assign the subjects to one of the three subgroups.

## Inclusion criteria

- Men and women
- Age between 18 and 50 years
- BMI between 28 and 35 kg/m2
- Non-smoking
- Normal general health (screening questionnaire)
- No medication that could interfere with the experiment
- Unrestrained eaters (F1 < 9)

## Exclusion criteria

- Age under 18 and over 50 years
- BMI under 28 and over 35 kg/m2
- Smoking
- High blood pressure (systolic > 140mmHg and/or diastolic > 90mmHg)
- Anaemia (Hb < 7.5 mmol/L)
- Recent blood donation (screening questionnaire)
- Diseases like diabetes, cardiovascular disease or renal disease (screening questionnaire)
- Medication use that could interfere with the experiment
- Women: pregnant or breastfeeding
- Food allergies
- Allergies for local anaesthetic
- Dietary restrained eaters (F1 > 9)
- Excessive physical activity
- Consumption of more than 2 alcoholic drinks per day
- Gain or loss of more > 5 kg in the 6 months prior to study entry
- Subjects who do not want to be informed about any health concerning exclusion criteria, like anaemia or blood pressure can not participate.

| --- | --- | --- | --- |
| **TT** | 37% | 43% | 25% |
| **TA** | 48% | 45% | 45% |
| **AA** | 15% | 12% | 30% |

**Table 1**. frequency distribution of the FTO rs993909 alleles in populations with different mean BMI (4, 26).

# TREATMENT OF SUBJECTS

## Investigational product/treatment

All subjects undergo a weight loss program, which consists of a very low calorie diet (VLED; Modifast) containing 2.1MJ/d for 2 months. There are no risks for the subjects in consuming the VLED (Modifast, together with the recommended fruit and vegetables) as the macronutrient composition and vitamins/minerals content meet the Dutch recommended daily allowance.

Deuterium is an isotope of water that naturally appears in the body. Drinking it does not expose the subject to any risks. The doubly labelled water is safe to use in humans since the water is labelled with stable isotopes. The concentrations of the samples are far below 10000 ppm or 1%, where effects on biological systems have been observed.

## Use of co-intervention (if applicable)

Not applicable

## Escape medication (if applicable)

Not applicable

# INVESTIGATIONAL MEDICINAL PRODUCT

Not applicable

# METHODS

## Study parameters/endpoints

### Main study parameter/endpoint

The role of the genetic background involved in weight regain through mechanisms including energy expenditure, physical activity and adipogenic capacity.

Energy expenditure (see fig 2, page 13, and page 21 and 22 for detailed description) will be determined via three measurements. First, the respiration chamber measurements, which will determine oxygen consumption and carbon dioxide production overnight to determine sleeping metabolic rate. Second, the ventilated hood measurements in the mornings to determine basal metabolic rate. And the last measurement is the use of doubly labelled water to determine total energy expenditure. These measurements will be performed before and after weight loss, and after weight maintenance.

Physical activity (see fig 2+3 on page 13+14, and page 20 for detailed description) will be determined via a triaxial accelerometer, which ensures movement registration sensitive to a wide range of body movements, thereby determining habitual physical activity. These measurements will be performed before and after weight loss, and after weight maintenance.

Adipogenic capacity (see fig 2, page 13, and page 21 for detailed description) will be determined via measurements on number and size of fat cells from fat biopsies. These measurements will be performed before and after weight loss, and after weight maintenance.

## Randomisation, blinding and treatment allocation

The allocation of subjects to the groups with a high or low predisposition for weight regain is based on the genetic profile (the FTO rs9939609 allele). 40 subjects homozygous for the A allele will be allocated to the group with high predisposition for weight regain. 40 subjects homozygous for the T allele will be allocated to the group with low predisposition for weight regain. All remaining subjects will be allocated to the group with a medium predisposition for weight regain (see also section 4.4 sample size calculation).

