## Study procedures

TFEQ

Eating behaviour is evaluated using in a Dutch translation of the three-factor eating questionnaire (TFEQ). This validated questionnaire consists of three subscales: cognitive restraint of eating, disinhibition of dietary restraint and emotional eating and perceived hunger (24).

Baecke questionnaire

Habitual physical activity is evaluated using a Dutch translation of the Baecke questionnaire. This questionnaire consists of three subscales: work activity, sports activity and non-sports leisure activity (27).

Blood samples

On the day of the screening a blood sample (10 ml) will be collected via vena puncture in the antecubital vein in a 10 ml EDTA tube. From the peripheral blood leukocytes from the blood DNA will be isolated and certain SNPs will be genotyped. Genotyping will be performed using commercially available TaqMan SNP genotyping assays according to the manufacturer’s protocol. The following SNPs will be determined:

- FTO rs9939609 A allele (4-8, 26, 28)
- MC4R rs7782313 C allele (29-32)
- PPAR2 Ala12 allele (9, 10, 15)
- ADRB2 Gly16 allele (33, 34)
- PLIN 11482 A allele (12, 13)
- UCP1 A3826 A allele (35, 36)

Subjects’ blood lipid profile (triacylglycerols (TAG), free fatty acids (FFA), total cholesterol, HDL, and LDL) and glucose homeostasis (glucose, insulin, and HbA1c) will be determined. For this, 10ml blood will be collected in an EDTA tube. In total 20 ml blood will be taken per subject ones. Blood samples will be stored at - 80C until analyses.

Body composition

Subjects’ body composition will be calculated from body volume and total body water using the combined equation of Siri (37). Body volume is measured with a BodPod. Total body water is measured with Deuterium dilution according to the Maastricht protocol (38). Subjects drink a Deuterium dilution (about 70 g with an enrichment of 5 atom% excess 2H) in the evening prior to the measurements after the collection of a baseline urine sample. The next morning after a 10-hour equilibration period, where subjects are not allowed to eat or drink, a second urine sample is collected.

Physical activity

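### The groups are defined by FTO rs9939609 alone, so the trial can conclude about FTO but not about a multi-gene profile or an established predisposition for weight regain

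*Protocol*

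**What the plan says.** The protocol describes the grouping variable in several places.

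- **Summary, study design.** Groups are stratified by the subjects' "genetic profile for established markers of postprandial responses in substrate utilization and habitual physical activity".
- **Section 7.2.** Allocation "is based on the genetic profile (the FTO rs9939609 allele". The rule for the first group is: "40 subjects homozygous for the A allele will be allocated to the group with high predisposition for weight regain". The low group is built the same way from 40 TT homozygotes. For everyone else the rule is: "All remaining subjects will be allocated to the group with a medium predisposition for weight regain". Section 4.4 gives the same AA and TT rule, with 120 subjects in the medium group.
- **Section 2 and section 7.1.1.** The objective speaks of predisposition groups formed from a genetic profile. The main endpoint is the role of the genetic background in weight regain. The outcomes named are body composition (section 2 only), energy expenditure, physical activity and adipogenic capacity.
- **Section 7.3.** Six SNPs are genotyped: FTO, MC4R, PPAR gamma 2, ADRB2, PLIN and UCP1. The UCP1 entry reads "UCP1 A3826 A allele".
- **Section 1.** For FTO, "The A allele is associated with increased body mass index (BMI) (6", and TA/AA carriers taken together show a reduced postprandial response in hunger and satiety.

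**The concern.** The labels claim more than the allocation rule delivers. A difference between the high and low groups is a difference between two homozygotes at one locus. Under the present objective and endpoint it could be read as a genetic mechanism of weight regain, and a null result could be read as no role for genetic predisposition. Neither reading follows from an FTO contrast, least of all if nobody has checked whether the 'high' group regained more weight.

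There is also a practical problem. The medium group is a remainder, not a genotype, so any three-group comparison mixes subjects who share a genotype with the low group into the group meant to lie between the extremes.

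**Working it through.** **1. The plan's own figures reproduce.** From section 4.4: 21 × 375² / (2068 − 1778)² + 0.96 = 35.11 + 0.96 = 36.07, so 36 per group. With 10% drop-out, 36 / 0.90 = 40. With AA assumed at 20%, 40 / 0.20 = 200. The medium group is 200 − 40 − 40 = 120. The arithmetic is not at issue.

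**2. Grouping basis, set side by side.**

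| Source | Basis |
| --- | --- |
| Summary | Markers of postprandial substrate utilisation and of habitual physical activity |
| Sections 4.4 and 7.2 | FTO genotype only |
| Section 1 on FTO | BMI, hunger and satiety |

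Section 1 gives FTO neither of the two roles in the Summary. The three SNPs that section 1 ties to physical activity (rs2267668, rs2076168, rs8192678) are not on the section 7.3 list.

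**3. Evidence on regain.** Section 1 reports greater regain in women carrying PPAR gamma 2 Ala12, and a higher frequency of ADRB2 Gly16 among people who regained. It reports nothing on regain for FTO. Both of the other SNPs are genotyped and neither enters allocation. The FTO appetite finding pools TA with AA, so it does not distinguish the 'high' group from the TA subjects in 'medium'.

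**4. How many 'medium' subjects are TT.** The inputs are the TT frequencies in Table 1 and the 40 TT taken for the low group. Surplus TT = 200 × frequency − 40.

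| Table 1 population | TT | TT in 200 | Surplus TT | Share of 120 |
| --- | --- | --- | --- | --- |
| Mean BMI 45 | 25% | 50 | 10 | 8% |
| Mean BMI 25.0 | 37% | 74 | 34 | 28% |
| Mean BMI 24 | 43% | 86 | 46 | 38% |

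The denominator of 120 assumes that the high group fills with exactly 40 AA. Taking each Table 1 column whole changes it:

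- At mean BMI 45 there are 60 AA, so 20 surplus AA join the 10 surplus TT, and 30 of 120 (25%) are not TA.
- At mean BMI 25.0 there are only 30 AA, and 'medium' is 34 TT + 96 TA = 130 (26% TT).
- At mean BMI 24 there are 24 AA, and 'medium' is 46 TT + 90 TA = 136 (34% TT).

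As a mid-range check, assume Hardy-Weinberg proportions with AA at 20%. Then TT is (1 − √0.20)² = 30.6%, or 61 of 200, which leaves 21 surplus TT.

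**5. Effect on a three-group comparison.** If a share w of 'medium' is TT and the rest is TA, the mean difference between medium and low is (1 − w) × (TA − TT). With w of 8%, 28% and 38%, the contrast keeps about 92%, 72% and 62% of its true size. This assumes that surplus TT subjects resemble those chosen for the low group and that there is no surplus AA.

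**6. UCP1.** Section 7.3 lists the A allele, whereas section 1 says that "GG homozygotes were more resistant to weight loss". For FTO, PPAR gamma 2, ADRB2 and PLIN, the listed allele is the one that section 1 presents as unfavourable. Section 1 does not discuss MC4R.

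**The case against.** Section 7.2 states openly that the profile is FTO. Using one SNP with known frequencies is a disclosed design choice, and section 1 introduces FTO as a well-known gene in weight management. One reference cited for FTO names resting metabolic rate in its title, and energy expenditure is a main parameter. All of this stands. None of it concerns regain, and it does not remove the conflict with the Summary.

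Some stronger readings are tempting but lack support:

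- *The trial cannot address regain.* Figures 2 and 3 show body weight measured in all groups after the diet and at 3 and 10 months of maintenance, and section 9.2 plans repeated-measures ANOVA. The comparison is available. It is only not named among the outcomes.
- *The five other SNPs will go unanalysed.* Section 9.2 plans simple and multiple regression without listing predictors, and that detail may properly sit in a statistical analysis plan.
- *The UCP1 entry damages the data.* Genotyping reads both alleles, section 7.3 does not call its alleles unfavourable, and no allele score is planned. The inconsistency matters only if a direction is later taken from that list.
- *Renaming the groups AA, TA and TT is enough.* It would mislabel the surplus TT subjects counted above.
- *The term predisposition should stand or fall by a significant regain difference.* The sample size rests on energy expenditure, at 290 / 375 = 0.77 SD, and not on regain. A non-significant result would not disprove predisposition.

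**Conclusion.** The point holds in a limited form. The protocol gives conflicting accounts of its grouping variable, and the operative one is a single SNP for which it cites no regain evidence. The AA-TT comparison is valid as a statement about FTO rs9939609. It does not extend to a multi-gene profile or to an established predisposition for regain.

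The measurable part is the make-up of the medium group. About 10 to 46 of its 120 members would share the low group's genotype, across the TT range of 25% to 43% in Table 1. This assumes 200 subjects with 40 AA. The study population has a BMI of 28 to 35, between the Table 1 populations, so the true figure is uncertain within that range. The AA-TT contrast is not affected by this mixing.

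**What to change.** 1. Reconcile the Summary, section 2, section 7.1.1 and section 7.2 so that the groups are described as FTO-defined, and limit the primary conclusion to FTO rs9939609. The SNP is written rs993909 in sections 1 and 4.4, and this can be corrected at the same time.
2. For outcomes measured in all 200 subjects, analyse by actual genotype (AA, TA, TT) and not by the high, medium and low labels.
3. Name weight change from the end of the diet to the end of maintenance, by FTO genotype, as an explicit analysis. Report it with a confidence interval beside the mechanism outcomes, because the sample size was not set for it.
4. Optionally, pre-specify one secondary regression of regain on the other genotyped SNPs. Fix each allele's direction beforehand, and reconcile section 1 with section 7.3 on UCP1.

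The cost is wording and a few lines of analysis specification on data already being collected, with no extra visits or samples. The downside is a narrower headline claim.
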